### Sample size

The primary outcome of this experiment is the PSQI score, and a two-sample t test for superiority by a margin will be adopted. Similar published studies have indicated that the mean PSQI scores of the EA and SA groups are 9.8 and 13.9, respectively, with standard deviations of 3.1 and 3.2. The SA group is expected to have a higher score than the EA group, with an expected score difference of 1.5. With a significance level of α = 0.025, power of 1-β = 0.9, and equal sample sizes of the SA and EA groups [21], the minimum sample size was calculated. According to the preset parameters, the “Two-Sample t Tests for Superiority by a Margin Allowing Unequal Variance” option in the Means menu of Power Analysis and Sample Size software (PASS; version 11; NCSS Statistical Software, Kaysville, UT, USA) was used for sample size calculation. A sample size of 32 was calculated for both groups. Considering a dropout rate of 20%, each of the three groups would require 40 participants. Therefore, 120 subjects will be included in the study to ensure the accuracy and scientific validity of the research results.

### Statistical analysis

In general, statistical involve a two-tailed approach, and any results that have a p value of less than 0.05 are considered statistically meaningful. Continuous data will be characterized by the mean ± standard deviation, median, highest value, and lowest value, while count and ordinal data will be represented via counts and percentages. The type of analysis used for between-group comparisons depends on the data distribution: paired-sample t tests or nonparametric tests will be used for continuous data, chi-square tests or Fisher’s exact test will be used count data, and nonparametric tests will be used for ordinal data. For comparisons of baseline values, paired-sample t tests or nonparametric tests will be used for continuous data, and nonparametric tests will be used for count data.

All EEG data will be processed using MATLAB (MathWorks, Inc., Natick, Massachusetts, USA). Graph theory analysis will be performed using the Gretna toolbox based on MATLAB. The analysis of brain network topological properties will employ graph theory methods. Specifically, the following steps will be used: segmentation according to the AAL template to divide the brain into 116 regions, computation of the average BOLD time series signals within each region, and calculation of Pearson correlation coefficients between each pair of regions. It will yield a 62 × 62 correlation matrix. The correlation matrix will then be converted into a binary matrix by applying a threshold r value (Pearson correlation coefficient) to construct a brain network. The topological properties of the brain network, including global efficiency, local efficiency, node degree, and node betweenness centrality, will be analyzed. Additionally, the relationships of topological properties with cognitive function and sleep quality scores will be examined through correlation analysis.

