**Methods:**

This study is divided into two parts. Sixteen individuals with chronic insomnia and 16 healthy controls of similar age and gender will be recruited in Study 1 to examine the brain network topology of individuals with chronic insomnia. Study 2 will be a randomized controlled trial with 120 chronic insomnia patients divided into three groups: Group A (electroacupuncture plus placebo drug), Group B (drug plus placebo electroacupuncture), and Group C (placebo electroacupuncture plus placebo drug). Participants will be exposed to 24 treatments over an 8-week period (3 times per week) and monitored for 12 additional weeks. The primary outcome measure will be changes in brainwave data from before to after the treatment. In addition, the Wisconsin Card Sorting Test and the Pittsburgh Sleep Quality Index will be utilized as secondary outcomes to measure from before to after treatment and during the follow-up. A correlation analysis will be conducted to explore links among modifications in brainwave patterns, Wisconsin Card Sorting Test scores, and Pittsburgh Sleep Quality Index scores. Additionally, any adverse events will be strictly monitored.

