**Discussion:**

Electroacupuncture may represent an alternative treatment for chronic insomnia, and this trial is expected to reveal the brain mechanism by which electroacupuncture improves cognitive function and sleep quality in chronic insomnia patients.

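### The PSQI test that sizes the trial has no visit and is not carried into the analysis section, whose blanket p<0.05 rule leaves up to 18 PSQI and WCST tests unranked and sets a different bar for success

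*Protocol article*

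**What the plan says.** - **Protocol article, Statistical analysis.** The general convention is "In general, statistical involve a two-tailed approach", and "any results that have a p value of less than 0.05 are considered statistically meaningful". No visit, contrast or scale is ranked, and none is called exploratory.
- **Sample size.** PSQI is called the primary outcome here, to be tested by a two-sample t test for superiority by a margin. The contrast is EA against SA: "The SA group is expected to have a higher score than the EA group". The inputs are that "the mean PSQI scores of the EA and SA groups are 9.8 and 13.9, respectively", SDs of 3.1 and 3.2, a figure of 1.5 points, a "significance level of α = 0.025" and "power of 1-β = 0.9". The result is 32 per group, or 40 after 20% dropout. No visit is given.
- **Abstract and Outcomes.** EEG is primary. PSQI and WCST "will be utilized as secondary outcomes to measure from before to after treatment and during the follow-up".
- **Table 1.** PSQI and WCST are collected at Weeks 0, 4, 8 and 20, so there are three post-baseline visits. The Follow-up section gives Week 20 the role of showing whether effects last.
- **Randomization and blinding.** Three arms at 1:1:1, so three pairwise contrasts are possible.
- **Abstract, Discussion.** "Electroacupuncture may represent an alternative treatment for chronic insomnia".

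**The concern.** The title announces a therapeutic effect on cognition and sleep quality, so the reader needs to know which clinical result would establish it. The sizing text goes part of the way: one scale, one contrast, one test and one alpha, but no visit. The section that governs the analysis drops all of that and applies a single threshold to every result.

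Two things follow. First, a Week 4 difference, a durability difference at Week 20 or a difference on WCST (no score named) would stand level with the test the trial was sized for. The 90% power belongs to that one PSQI test, while the error rate belongs to the whole set. Second, the article holds two success criteria for the same comparison, one with a margin and one without. An observed PSQI difference lying between the two bars would succeed under one section and fail under the other.

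**Working it through.** **1. Reproduce the stated sample size.** Inputs from the Sample size section: means 9.8 and 13.9, SDs 3.1 and 3.2, 1.5 points, alpha 0.025, power 0.90.

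- Difference: 13.9 − 9.8 = 4.1. Reading 1.5 as the margin, the distance to detect is 4.1 − 1.5 = 2.6.
- The noncentral-t (Welch) calculation at one-sided 0.025 gives power 0.892 at 31 per group and 0.901 at 32. So n = 32, as stated.
- 32 / (1 − 0.20) = 40, and 3 × 40 = 120, as stated.
- Other readings do not fit (normal approximation, which gives 31 for the reading above): two-sided 0.025 gives 37; one-sided 0.05 gives 26; a difference of 4.1 with no margin gives 13; a difference of 1.5 gives 93.

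The sizing is therefore a margin test at one-sided 0.025, with 1.5 as the margin, although the text words 1.5 as an expected difference. One-sided 0.025 is consistent with two-sided 0.05, so the alpha is not in dispute.

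**2. Compare the two success rules for PSQI, A versus C** (32 evaluable per arm).

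- SE = sqrt((3.1² + 3.2²) / 32) = sqrt(19.85 / 32) = 0.788.
- Critical value: t(0.975, 62 df) = 2.00.
- Statistical analysis rule (no margin): 2.00 × 0.788 ≈ 1.6 points observed.
- Sample size rule (margin 1.5): 1.5 + 2.00 × 0.788 ≈ 3.1 points observed.

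**3. Count what the blanket rule permits.** 2 scales × 3 contrasts × 3 visits = 18 tests, of which 9 are PSQI. This takes a single WCST score; several scores would add more.

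**4. Error rate under no effect anywhere.** If the tests were independent, 1 − 0.95^18 = 60% and 1 − 0.95^9 = 37%. They are not independent, so the rates were simulated: three arms of 32, three visits, two scales, two-sided t tests at 0.05 with no margin, 10,000 runs per setting. The article gives no correlations. The assumed values are 0.3 to 0.9 between visits and 0 to 0.5 between scales.

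| Set of tests | Tests | Chance of at least one false positive |
|---|---|---|
| PSQI and WCST, all contrasts, all visits | 18 | 33-52% |
| PSQI, all contrasts, all visits | 9 | 19-31% |
| PSQI and WCST, A vs C, all visits | 6 | 15-26% |
| PSQI, A vs C, all visits | 3 | 8-14% |
| False result favouring EA over sham or drug | 12 | 13-22% |
| False result favouring EA over sham only | 6 | 8-14% |

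The last two rows count one direction only, for which the nominal rate of a single test is 2.5%.

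**5. Error and power once one test decides.** With PSQI, A versus C, at one visit as the sole first test, the false-positive rate in favour of EA is 2.5%, and 32 per group keeps power 0.90 with the margin. If PSQI had to share alpha (one-sided 0.0125), power at 32 would fall to 0.84. That is a reason to prefer a fixed order.

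**The case against.** **The contrast is named.** A reader might infer that the plan has no deciding clinical contrast at all. It does not support that: the Sample size section gives PSQI, EA versus SA, a test and an alpha, and its figure reproduces. What stands is that the visit is missing and that the analysis section does not take the test up.

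**The 18 tests are not listed.** A reader might also infer that 18 tests are planned. Table 1 is a collection schedule, the analysis section speaks only of between-group comparisons, and its threshold is introduced as a general convention. The 18 are what the rule allows. The narrowest case does not depend on them: granting PSQI, A versus C, alone, the open visit still takes 5% to 8-14%.

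**A chance benefit is not likely.** The 33-52% counts results in either direction, including drug against sham and results against EA. A false result favouring EA is 13-22%, which is inflated but not more likely than not.

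**The margin protects PSQI if it is used.** With a 1.5-point margin and no true difference, the chance of a false PSQI success is about 0.00006 per test. The PSQI figures above apply only if the general rule replaces the margin test. Because the analysis section omits the margin, that reading is open, and it is why the two sections must be reconciled.

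**An unseen analysis plan may rank the tests.** The order of secondary tests and the choice of WCST score are commonly left to it, and their absence alone would be no finding. What stands is what the article does state: a blanket rule that does not match its own sizing test, and PSQI primary in one section and secondary in others.

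**The wording on an alternative treatment is hedged.** It claims no equivalence with the drug, and the 1.5 points come from the sham comparison, so they cannot serve as a comparability margin for A versus B.

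**Conclusion.** The point holds in this form. The trial is sized on a specific PSQI test with no visit. The analysis section replaces that test with an unranked p<0.05 rule, and the two give different bars for success, about 3.1 and 1.6 points.

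Followed as written, the rule raises the error rate above 5% in every setting tried: from 8-14% when only the visit is open to 33-52% when every permitted test counts. For false claims favouring EA, 13-22% is roughly five to nine times the 2.5% of a single test.

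These figures rest on the assumed correlations, one WCST score, 32 evaluable per arm and no margin. The two bars rest on the protocol's SDs and on 1.5 being the margin. This should be corrected; it does not call the sample size into question.

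**What to change.** In the Statistical analysis section, for the clinical scales:

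1. Name PSQI, Group A versus Group C, at Week 8 as the deciding clinical test, using the margin test of the Sample size section at one-sided 0.025. If the margin is to be dropped, say so and restate the power; the 90% belongs to the margin test.
2. State whether PSQI or EEG is the trial's primary outcome and make the Abstract, Outcomes and Sample size sections agree.
3. Then test in fixed order: one named WCST score, A versus C, Week 8; PSQI, A versus C, Week 20; the same WCST score, A versus C, Week 20. Claim only up to the first non-significant step.
4. Label Week 4 results and the B versus C and A versus B contrasts exploratory. Report A versus B as an estimate with a 95% CI.

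The cost is wording: no added patients, visits or measurements, and 32 evaluable (40 randomised) per group stays as it is. The change should be made and dated before anyone sees results by group. Recruitment was scheduled to end in December 2024, so whether that is still possible has to be confirmed. The price is that exploratory results, and steps after a failure, cannot be claimed as confirmatory.

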### Outcomes

#### Primary outcomes

EEG data will be the primary outcome measure and recorded before and after the treatment. During EEG recording, subjects will be in a quiet room and wear a 64-lead Waveguard Original (CA-208, ANT neuroo, the Netherlands) Ag/AgCl EEG cap, keeping their eyes closed. EEG data will be collected with an electrode distribution according to the international 10–20 standard. EEG recordings will be performed with the company’s eego64 acquisition software, version 1.8.2, with the CPz and AFz electrodes used as the reference and ground electrodes, respectively. The sampling frequency will be 1000 Hz, and the electrode impedance will be reduced to less than 5 kΩ for each recording.

The preprocessed data will be transformed into a binary matrix to measure brain network parameters, including global efficiency, local efficiency, node degree, and node betweenness centrality.

Each index will be calculated as follows:

Global efficiency

$${E}_{\text{g}\text{l}\text{o}\text{b}}=\frac{1}{N\left(N-1\right)}{\sum }_{i\ne \dot{J}{\epsilon}V}\frac{1}{{l}_{ij}}$$

where $$V$$ is the set of all nodes, and $${l}_{ij}$$is the shortest path length of node $$i$$ and node $$j$$ (i.e., the path with the least number of edges).

b.Local efficiency

$$E\left(i\right)=\frac{1}{{N}_{Gi}\left({N}_{Gi}-1\right)}{\sum }_{\dot{J}\ne k{\epsilon}{G}_{i}}\frac{1}{{l}_{jk}}$$

$${E}_{loc}=\frac{1}{N}{\sum }_{i{\epsilon}V}E\left(\dot{i}\right)$$

where $$E\left(i\right)$$ represents the local efficiency of node $$\dot{i}$$, $${G}_{i}$$ is the subgraph formed by the neighbors of node $$\dot{i}$$, and $${l}_{jk}$$ denotes the shortest path length of node j and node $$k$$.

c.Degree.

Degree refers to the number of edges connected to a node. To analyze the constructed brain network and the neuromodulation effect of acupuncture, the node degree was selected for objective evaluation and analysis.

d.Betweenness centrality

$${N}_{bc}\left(i\right)={\sum }_{\dot{J}\ne i\ne k{\epsilon}G}\frac{{\sigma }_{jk\left(i\right)}}{{\sigma }_{jk}}$$

where $${\sigma }_{jk}$$ denotes the number of shortest paths from node $$\dot{J}$$ to node $$k$$, and $${\sigma }_{jk\left(i\right)}$$denotes the number of shortest paths that pass through node $$\dot{i}$$.

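### Any p below 0.05 counts, but the EEG primary outcome has four network parameters and no lead parameter, node or contrast, so its family-wise error is uncontrolled

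*Protocol article*

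**What the plan says.** The Statistical analysis section of the protocol article opens with "In general, statistical involve a two-tailed approach" and then sets its only decision rule: "any results that have a p value of less than 0.05 are considered statistically meaningful". It states no adjustment, order of testing or exploratory label.

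Under Primary outcomes, "EEG data will be the primary outcome measure and recorded before and after the treatment". The recordings are reduced to "brain network parameters, including global efficiency, local efficiency, node degree, and node betweenness centrality". Degree and betweenness belong to individual nodes. Global efficiency is a whole-brain figure. Local efficiency is defined node by node and then averaged over the brain. The Statistical analysis section repeats the list without ranking it: "The topological properties of the brain network, including global efficiency, local efficiency, node degree, and node betweenness centrality, will be analyzed". It adds correlations of these properties with the cognitive and sleep scores.

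Two further statements affect how many tests there are:

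- **Node count.** The Statistical analysis section describes "segmentation according to the AAL template to divide the brain into 116 regions" and then a correlation matrix of 62 by 62.
- **Primary outcome.** The Sample size section names the PSQI score as primary, whereas the Abstract and the Outcomes section name EEG and list the PSQI as secondary.

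Three groups are randomized 1:1:1, and the article does not list the between-group contrasts. The dorsolateral prefrontal cortex is singled out in the Background and the Discussion, but testing is not restricted to it.

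**The concern.** A rule that accepts every p value below 0.05 controls error for one test. Here it is attached to a primary outcome that is a family of tests, and the article does not say which member decides the trial. The family has at least four members in one contrast, and well over a hundred if the nodal parameters are examined at each node.

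The stated aim is to explain how electroacupuncture works in the brain. Under this rule, a few scattered nodal differences could be reported as that mechanism although electroacupuncture had changed nothing. A reader of the results could not tell a planned finding from the best of many.

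**Working it through.** **1. The plan's own figures.** The article gives no family-wise error to reproduce. Its only other significance level, 0.025, belongs to the PSQI sample size. That calculation reproduces with a one-sided unequal-variance t test: difference 13.9 − 9.8 = 4.1, less 1.5 used as a superiority margin, gives 2.6. With SDs 3.1 and 3.2, power is 0.901 at 32 per group and 0.892 at 31. Then 32/0.8 = 40 and 3 × 40 = 120. So 32 evaluable patients per arm is a fair basis for what follows, but this level does not protect the EEG tests.

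**2. Size of the family for one contrast, electroacupuncture versus double placebo (Group A versus Group C).** Only this contrast tests the null of no electroacupuncture effect whether or not the drug works.

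- Four parameters, one summary figure each: 4 tests.
- Two whole-brain figures plus degree and betweenness at 62 nodes: 2 + 2 × 62 = 126 tests.
- The same with 116 regions: 2 + 2 × 116 = 234 tests.

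**3. Independent tests, all nulls true.** The chance of at least one p below 0.05 is 1 − 0.95^k, and the expected number is 0.05k.

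| k | Chance of at least one | Expected number |
|---|---|---|
| 4 | 1 − 0.95^4 = 18.6% | 0.2 |
| 126 | 1 − 0.95^126 = 99.8% | 6.3 |
| 234 | above 99.9% | 11.7 |

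**4. Correlated tests.** Parameters computed from one thresholded matrix will be correlated, and the article does not say how strongly. A simulation therefore assumed a range: 32 patients per arm, normal measures with a common correlation, two-sided t tests at 0.05, 1,500 runs, A versus C only.

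| Correlation | 4 measures | 126 measures |
|---|---|---|
| 0.3 | 17% | 98% |
| 0.5 | 17% | 84% |
| 0.7 | 14% | 53% |
| 0.9 | 10% | 23% |

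Monte Carlo error is about one percentage point at 84% (√(0.84 × 0.16/1500) = 0.009). Correlation does not change the expected count: false positives come in clusters, less often but more at a time. With 126 measures the simulated mean stayed between 6.2 and 6.9.

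**5. What control would require.** Bonferroni thresholds are 0.05/4 = 0.0125 for four tests and 0.05/126 = 0.0004 for 126. One named measure in one named contrast needs no correction.

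**The case against.** The strongest reply is that this is a condensed article. An analysis plan that is not shown may hold a node-level correction, an order of contrasts and exploratory labels, and the significance sentence begins with a general qualifier. Part of this stands: the absence of correction details is not itself a fault. But the article goes further than silence. It states a rule covering any result and attaches it to a primary outcome with no lead variable. The qualifier introduces the two-tailed approach and, even if read over the whole sentence, names no exception.

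Three stronger readings are tempting and are not supported:

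- **A false mechanism finding is almost certain.** This needs every node to be tested separately and the measures to be no more than moderately correlated. The article states neither. With four measures, or with 126 at correlation 0.9, the risk is far below certainty.
- **The expected count should be tripled for three arms.** The article lists no contrasts. Drug versus double placebo cannot produce an electroacupuncture finding, and electroacupuncture versus drug is a true null only if the drug also does nothing. The single-contrast figure is the relevant one.
- **The trial is too small to show electroacupuncture as good as the drug.** The Abstract says only that "Electroacupuncture may represent an alternative treatment for chronic insomnia". No non-inferiority or equivalence hypothesis is stated. The 1.5 points serve as a superiority margin against sham, so borrowing them for the drug comparison would fault a test that the protocol never proposes.

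The split into two whole-brain and two nodal parameters is also a reading. If local efficiency were tested node by node as well, the family would be larger.

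**Conclusion.** The point holds in a limited form. The 0.05 rule, combined with an EEG primary outcome that has no lead parameter, node or contrast, leaves family-wise error uncontrolled. For electroacupuncture versus double placebo it runs from about 19% (four independent summary parameters) to nearly 100% (all nodes, independent). Correlation brings the all-node figure down to about 84% at 0.5 and 23% at 0.9, and the four-measure figure to about 10% at 0.9. Every case examined lies above 5%.

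These figures assume that electroacupuncture has no effect on any measure. The simulated ones also assume 32 evaluable patients per arm and a common correlation, for which the article gives no value. The 126-test figure uses 62 nodes; until that is reconciled with 116 regions, the size of the family is itself undefined. How many nodes will be tested is not stated, so the upper figures show what the rule permits and do not predict what the analysts will do. The point is worth correcting, but it does not invalidate the design.

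**What to change.** Before any analysis by group:

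1. Reconcile the primary outcome (EEG under Primary outcomes, PSQI under Sample size) and the node count (116 or 62). The steps below depend on both.
2. Name one confirmatory contrast, electroacupuncture versus double placebo, on one pre-specified primary measure. Limit the 0.05 decision rule to that test.
3. For EEG, name one lead parameter. It could be a whole-brain measure or a measure at the dorsolateral prefrontal node that the authors already single out; that choice is theirs.
4. Apply a family-wise correction such as Holm to the other summary parameters. With three of them, the smallest p would be compared with 0.05/3 = 0.0167. Control the false discovery rate at 5% across nodes.
5. Label the remaining contrasts and the correlations with cognitive and sleep scores exploratory, and report them as estimates with 95% confidence intervals.

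The cost is a few sentences and minor analysis work, with no change to recruitment or sample size. The downside is fewer nominally significant nodal results.

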### Randomization and blinding

The “Proc plan” feature of SAS 9.3(SAS Institute Inc., Cary, NC, USA) will be employed to create the necessary random allocation plan for the study. Eligible subjects will be assigned to Group A (electroacupuncture plus placebo drug), Group B (drug plus placebo electroacupuncture), or Group C (placebo electroacupuncture plus placebo drug) at a ratio of 1:1:1. All patients will be seen by appointment. During the acupuncture intervention, which will be completed in a quiet, separate treatment room to avoid contact and communication between patients in different groups, the therapist will instruct the patient to close their eyes. Only the acupuncturist performing the needle insertion throughout the trial will be aware of the patient’s group allocation. The subjects, evaluators of therapeutic effects, and individuals conducting the statistical analysts will be blinded to group allocation.

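### The article names paired-sample t tests for comparing independent randomized arms, which does not fit the parallel design and conflicts with the two-sample test used for sizing

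*Protocol article*

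**What the plan says.** The Statistical analysis section gives the rule for continuous outcomes: "The type of analysis used for between-group comparisons depends on the data distribution: paired-sample t tests or nonparametric tests will be used". The sentence after it reads: "For comparisons of baseline values, paired-sample t tests or nonparametric tests will be used for continuous data". The section names no independent-samples t test, analysis of variance or covariance model, and it does not limit the paired test to within-arm change or to Study 1.

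The Abstract describes Study 2 as "120 chronic insomnia patients divided into three groups", and Randomization and blinding assigns patients "at a ratio of 1:1:1". No crossover, matching or pairing between arms is described.

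The Sample size section says that "a two-sample t test for superiority by a margin will be adopted" and names the software option "Two-Sample t Tests for Superiority by a Margin Allowing Unequal Variance".

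**The concern.** A paired t test needs a natural link between each value in one sample and one value in the other. Patients in Groups A, B and C have no such link. The stated rule can be carried out in two ways, and neither gives a well-defined comparison of the arms.

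- **Pairing across arms.** Someone must decide which Group A patient is set against which Group C patient. The plan gives no rule, so the p value is not reproducible. With unequal completer numbers, some patients have no partner.
- **Before-after testing within each arm.** This is the usual use of a paired test, but it asks whether an arm changed, not whether the arms differ.

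The rule covers all continuous outcomes: the EEG network measures, called primary under Outcomes, and the PSQI, called primary under Sample size. For the PSQI there is also a direct conflict with the test adopted for sizing.

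**Working it through.** **1. Which test reproduces the stated sample size?** Inputs from the Sample size section: "the mean PSQI scores of the EA and SA groups are 9.8 and 13.9, respectively"; SDs 3.1 and 3.2; a value of 1.5, called an expected difference but working as the margin; alpha 0.025, taken as one-sided; power 0.90.

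- Distance beyond the margin: (13.9 − 9.8) − 1.5 = 2.6.
- Normal approximation: n = (1.960 + 1.282)² × (3.1² + 3.2²) / 2.6² = 10.51 × 19.85 / 6.76 = 30.9, so 31.
- Noncentral t with Welch degrees of freedom (about 62): n = 32, power 0.901. This matches the stated 32.
- Dropout: 32 / 0.80 = 40 per group, and 3 × 40 = 120. Both match.
- Readings that do not give 32: two-sided 0.025 with 2.6 gives 37 to 38; a difference of 1.5 with no margin gives 93 to 94; a difference of 4.1 with no margin gives 13 to 14; a paired test with 2.6 gives 33.

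The sizing therefore rests on the independent two-sample test.

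**2. What does a paired test on 32 arbitrary pairs cost?** With unrelated pairs the standard error is the same, √(19.85 / 32) = 0.788, so the noncentrality is 2.6 / 0.788 = 3.30. Only the degrees of freedom change, from about 62 to 31. Power becomes 0.892 against 0.901.

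Simulation (40,000 trials, 32 per arm, independent normal data, two-sided 0.05):

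| | Paired, blind to outcome | Welch |
|---|---|---|
| Type I error | 0.048 | 0.047 |
| Power at 2.6 | 0.893 | 0.901 |

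The mean difference was unbiased (2.60 for a true 2.6).

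**3. How far does the result depend on the pairing?** In one simulated data set (true difference 1.6), 5,000 random re-pairings gave p values from 0.000004 to 0.017. The Welch test gives a single value, 0.0017. Every pairing fell below 0.05 in that data set, so the decision would not have changed there; with data nearer the threshold it could. If patients are paired after sorting each arm by outcome, type I error rises to about 0.67.

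**4. Unequal completers.** The plan allows for 20% dropout. If, for illustration, 33 patients complete in A and 30 in C, at most 30 pairs exist and three patients are discarded.

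**5. The within-arm reading.** Suppose every arm improves by the same 2 points (assumed), with SD 3.15 and a pre-post correlation of 0.5 (assumed). The SD of change is √(2 × 3.15² × 0.5) = 3.15, and each arm is significant about 94% of the time with no treatment effect (74% for 1.5 points, above 99% for 3). This shows only that the test does not address the comparison between arms.

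**The case against.** The strongest reply is that this is a slip for independent-sample. In the same sentence, chi-square and Fisher's exact tests are tests for independent groups, the nonparametric option is not called paired, and the Sample size section names a valid two-sample test. This is plausible, and it means that the article contradicts itself on the PSQI rather than lacking any valid test. It does not remove the point: the paired test is named twice and nothing in the article corrects it. For the EEG and WCST outcomes, no other parametric test between arms is given.

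A reader might infer that the stated analysis cannot validly estimate the treatment effect. That goes too far. With equal arms paired blind to outcome, the estimate is unbiased, type I error is near nominal, and about one percentage point of power is lost.

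A reader might also infer a high risk, up to 25%, of finding A significant and C not when both improve equally. The article nowhere proposes to conclude in that way. The 25% is the ceiling of p(1 − p), reached at a within-arm power of one half; with 32 per arm it is about 8% for a change of 0.1 SD and 5% for 0.65 SD.

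Nor does the PSQI entry limit of 8 imply much regression to the mean. The limit lies (13.9 − 8) / 3.2 = 1.84 SD below the sham mean in the Sample size section. If patients resemble that group and scores are normal, the expected regression is about 0.02 to 0.05 SD for correlations of 0.7 to 0.3.

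On Study 1, the Trial design section describes the 16 controls as corresponding to the 16 patients. Individual matching is neither stated nor ruled out, so a paired test there is not shown to be wrong.

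**Conclusion.** The point holds as an error in a stated rule. The test named for between-group and baseline comparisons of continuous data does not fit three independent randomized arms, and it conflicts with the independent two-sample test that underlies the 32 per group. The consequence is an undefined or irreproducible comparison, possible loss of unpaired patients, or, on the within-arm reading, no comparison of arms.

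The measurable cost is small if pairing is blind to outcome (power about 0.89 against 0.90, under normal independent data and the sizing assumptions). It becomes serious only if the pairing is informed by outcome. The sample size of 32, 40 and 120 stands. The unspecified nonparametric option is not shown to be wrong, and the one-sided 0.025 used for sizing is compatible with the two-sided 0.05 used for analysis.

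**What to change.** In the Statistical analysis section, replace the paired-sample t test for between-group and baseline comparisons with an independent-groups comparison consistent with the Sample size section. State that any nonparametric alternative is also for independent groups, and say whether the 1.5-point margin will be tested.

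For outcomes, the preferred form is analysis of covariance of the week-8 value on arm and baseline value, reporting the A−C, B−C and A−B differences with 95% confidence intervals. The covariance model is a recommendation; an independent-groups test alone would remove the error. Keep paired tests only to describe change within an arm. In Study 1, use independent-sample tests unless controls are individually matched; if they are, say so.

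The cost is a change of wording. Table 1 already schedules the PSQI, WCST and EEG at baseline and week 8, so no extra patients or visits are needed. The change should be made before any unblinded analysis.
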